|                                                                                                                                                                                                                                                                                                                                                                                                                                                                                                  | When I am happy and celebrating                                                                                    | 1   2   3   4   5 |
|                                                                                                                                                                                                                                                                                                                                                                                                                                                                                                  | When I am very angry about something or someone                                                                    | 1   2   3   4   5 |
|                                                                                                                                                                                                                                                                                                                                                                                                                                                                                                  | When I would experience an emotional crisis, such as an accident or death in the family                            | 1   2   3   4   5 |
|                                                                                                                                                                                                                                                                                                                                                                                                                                                                                                  | When I see someone smoking and enjoying it                                                                         | 1   2   3   4   5 |
|                                                                                                                                                                                                                                                                                                                                                                                                                                                                                                  | When I realize that quitting smoking is an extremely difficult task for me                                         | 1   2   3   4   5 |
|                                                                                                                                                                                                                                                                                                                                                                                                                                                                                                  | When I am craving a cigarette                                                                                      | 1   2   3   4   5 |
|                                                                                                                                                                                                                                                                                                                                                                                                                                                                                                  | When I first get up in the morning                                                                                 | 1   2   3   4   5 |
|                                                                                                                                                                                                                                                                                                                                                                                                                                                                                                  | When I need to lift my spirits                                                                                     | 1   2   3   4   5 |
|                                                                                                                                                                                                                                                                                                                                                                                                                                                                                                  | With friends at a party                                                                                            | 1   2   3   4   5 |
|                                                                                                                                                                                                                                                                                                                                                                                                                                                                                                  | When I am extremely anxious or depressed                                                                           | 1   2   3   4   5 |
|                                                                                                                                                                                                                                                                                                                                                                                                                                                                                                  | When I am stressed                                                                                                 | 1   2   3   4   5 |

|                                                                                                                                                                                                                                                                                                                                                                        |                                                                                                        |                   |
|------------------------------------------------------------------------------------------------------------------------------------------------------------------------------------------------------------------------------------------------------------------------------------------------------------------------------------------------------------------------|--------------------------------------------------------------------------------------------------------|-------------------|
|                                                                                                                                                                                                                                                                                                                                                                        | When I realize I haven't smoked for a while                                                            | 1   2   3   4   5 |
| 
Pros and Cons
 
The following statements represent different opinions about smoking.
 
19. Please rate HOW IMPORTANT each statement is to you according to the following 5-point scale with
 
5 = Extremely important   4 = Very Important   3 = Moderately important   2 = Slightly important
1 = Not important
 |                                                                                                        |                   |
|                                                                                                                                                                                                                                                                                                                                                                        | Smoking cigarettes is pleasurable                                                                      | 1   2   3   4   5 |
|                                                                                                                                                                                                                                                                                                                                                                        | My smoking affects the health of others                                                                | 1   2   3   4   5 |
|                                                                                                                                                                                                                                                                                                                                                                        | I like the image of a cigarette smoker                                                                 | 1   2   3   4   5 |
|                                                                                                                                                                                                                                                                                                                                                                        | Others close to me would suffer if I became ill from smoking                                           | 1   2   3   4   5 |
|                                                                                                                                                                                                                                                                                                                                                                        | I am relaxed and therefore more pleasant when smoking                                                  | 1   2   3   4   5 |
|                                                                                                                                                                                                                                                                                                                                                                        | Because I continue to smoke, some people I know think I lack character                                 | 1   2   3   4   5 |
|                                                                                                                                                                                                                                                                                                                                                                        | If I try to stop smoking, I'll be irritable and a pain to be around                                    | 1   2   3   4   5 |
|                                                                                                                                                                                                                                                                                                                                                                        | Smoking cigarettes is hazardous to my health                                                           | 1   2   3   4   5 |
|                                                                                                                                                                                                                                                                                                                                                                        | My family and friends like me better when I am happily smoking than when I am miserable trying to quit | 1   2   3   4   5 |
|                                                                                                                                                                                                                                                                                                                                                                        | I'm embarrassed to have to smoke                                                                       | 1   2   3   4   5 |
|                                                                                                                                                                                                                                                                                                                                                                        | I like myself better when I smoke                                                                      | 1   2   3   4   5 |
|                                                                                                                                                                                                                                                                                                                                                                        | My cigarette smoking bothers other people                                                              | 1   2   3   4   5 |
|                                                                                                                                                                                                                                                                                                                                                                        | Smoking helps me concentrate and do better work                                                        | 1   2   3   4   5 |
|                                                                                                                                                                                                                                                                                                                                                                        | People think I'm foolish for ignoring the warnings about cigarette smoking                             | 1   2   3   4   5 |
|                                                                                                                                                                                                                                                                                                                                                                        | Smoking cigarettes relieves tension                                                                    | 1   2   3   4   5 |
|                                                                                                                                                                                                                                                                                                                                                                        | People close to me disapprove of my smoking                                                            | 1   2   3   4   5 |
|                                                                                                                                                                                                                                                                                                                                                                        | By continuing to smoke, I feel I am making my own decisions                                            | 1   2   3   4   5 |
|                                                                                                                                                                                                                                                                                                                                                                        | I'm foolish to ignore the warnings about cigarettes                                                    | 1   2   3   4   5 |

|  |                                                                |           |
|--|----------------------------------------------------------------|-----------|
|  | After not smoking for a while, a cigarette makes me feel great | 1 2 3 4 5 |
|  | I would be more energetic right now if I didn't smoke          | 1 2 3 4 5 |

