### **Hypothesis:**

The BSMART intervention (SBIRT and varenicline) will

- i. Increase the proportion of smokers able to quit smoking
- ii. Increase the number of attempts to quit smoking
- iii. Increase the length of abstinence in failed quit attempts
- iv. Decrease the number of cigarettes smoked every day
- v. Decrease the number of days of using combustible products within the past month
- vi. Decrease the number of days of using combustible products within the past three months in people exposed to the intervention as compared to people in the control phase

**Potential Impact:** Addressing the syndemic between tobacco use and HIV infection in a coordinated manner aligns with the NIH HIV/AIDS priorities for effective cancer control among PLWH in a high HIV prevalence setting. This study is significant because it integrates smoking cessation interventions, which are lacking in sub-Saharan Africa (SSA), into a real-world HIV care system that has been underpinned by a robust PEPFAR/CDC program and leverages long-standing partnerships with Ministry of Health and Wellness and the University of Botswana's Anti-tobacco Network for population, health system, and policy level impact.

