#### Secondary Outcomes:

- Quit attempts
- Length of successful quitting during each attempt
- Number of cigarettes currently smoked, and
- Number of days of using combustible tobacco products for at least 24 hours within the past month and the last 3 months.

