### Estimating process and outcome measures

All procedures will be conducted according to the local standards of routine clinical care. The following measures will be utilized:

1. **Baseline Demographic Information:** Baseline information will be abstracted from the HIV medical records and collected using a questionnaire. Baseline information will include demographics, medical history, laboratory values measured as part of HIV care (e.g. viral load, CD4), antiretroviral (ARV) history and ART treatment regimen (for current patients), and ART treatment start date. Because of high viral load suppression and high retention rate in this population, we will not be analyzing HIV treatment variables as mediators or outcomes.
2. **5”A”s (SBIRT) checklist:** This checklist will be completed by the LHW case managers and will serve to document the delivery of the intervention. A 10% random sample of the completed 5”A”s checklist will be reviewed by [name] during the time that a site is engaged in the intervention to ensure fidelity to the study intervention.
3. **Intake Smoking History Questionnaire** will measure length of smoking, use of other tobacco products, quit attempts, length of longest quit attempt, and smokers in the immediate living environment.
4. **Follow-up Smoking Use Questionnaire** will measure 7-day and 30-day point prevalence abstinence, number of cigarettes smoked (if not abstinent), stage of change and readiness to quit (if not abstinent), length of longest period of abstinence since last evaluation, use of varenicline, side effects, reasons for using or not using varenicline, and length of varenicline use.

5. **Stages of Change Algorithm** and **the Readiness Ruler**, will be used at baseline and follow-up to determine each individual's stage of change for quitting tobacco.
6. **Smoking Abstinence**: Abstinence will be based on self-reported 7-day point prevalence abstinence confirmed by expired CO < 6 ppm. Abstinence criteria must be met in participant Month 6 or at an earlier study week and maintained through participant Month 6 to be considered a responder. We will use coVita CO Smokerlyzer, a single-breath point-of-care tool designed specifically for use in smoking cessation programs and clinics.

For those who agree to be treated with varenicline:

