| The first one in The morning                                           | 1                                                                                                                                                                                               |                                                                                                                                                                                                                                                                                            |                              |        |               |   |             |   |              |   |               |   |
| All others                                                             | 0                                                                                                                                                                                               |                                                                                                                                                                                                                                                                                            |                              |        |               |   |             |   |              |   |               |   |

|                                                                                                                                                        |                                                                                                      |            |                |
|--------------------------------------------------------------------------------------------------------------------------------------------------------|------------------------------------------------------------------------------------------------------|------------|----------------|
| 2d.                                                                                                                                                    | How many cigarettes do you smoke per day?                                                            | 10 or less | 0              |
|                                                                                                                                                        |                                                                                                      | 11 – 20    | 1              |

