| We are going to ask you some questions about your smoking behavior                                                                                                                       |                                                                                       |                                                                                                                                                                                                                |
| 1.                                                                                                                                                                                       | Have you smoked a cigarette, even a puff, during the past 30 days?                    |  Yes
 No                                                                                                                                                    |
| 2.                                                                                                                                                                                       | Have you smoked a cigarette, even a puff, during the past 7 days?                     |  Yes
 No                                                                                                                                                    |
| 3.                                                                                                                                                                                       | Are you currently smoking regularly?

If yes, how many cigarettes a day? |  Yes
 No
_____ cigarettes                                                                                                                                |
| 4.                                                                                                                                                                                       | How many days of the week do you smoke?                                               |  7
 6
 5
 4
 3
 2
 1 |

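### Baseline cigarettes per day is recorded only in four bands while follow-up records a number, so change from baseline and baseline adjustment are available only at band level

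*Protocol*

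**What the plan says.** Cigarette consumption appears in four places in the protocol.

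- **Hypothesis iv:** the intervention will "Decrease the number of cigarettes smoked every day". The list of hypotheses closes with the comparison that applies to it: "in people exposed to the intervention as compared to people in the control phase".
- **Secondary Outcomes:** the list includes "Number of cigarettes currently smoked, and" other items. This is a current level. No change from baseline is named.
- **Intake, Appendix B3, item 2d:** "How many cigarettes do you smoke per day" is a scored Fagerstrom item with four tick-box bands: 10 or less, 11–20, 21–30, 31 or more. No other intake item shown asks for a count. The description under Estimating process and outcome measures says the intake form "will measure length of smoking, use of other tobacco products, quit attempts, length of longest quit attempt, and smokers in the immediate living environment", with no daily count in the list.
- **Follow-up, Appendix B4, item 3:** participants who say they are smoking regularly are asked "If yes, how many cigarettes a day", with space for a number. The same description section lists "number of cigarettes smoked (if not abstinent") for this form.

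Tables 2 and 3 schedule the follow-up questionnaire at weeks 4, 12 and 24 in both phases, and not at baseline. Breath CO is scheduled at baseline, week 12 and week 24 in both phases.

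**The concern.** A named secondary outcome is measured finely at follow-up, but its baseline value is known only coarsely. In an individually randomised trial this would mainly cost precision. Here facilities, not people, are randomised, and the 375 control and 375 implementation participants are different people. Within a facility they enrol in successive 12-month periods. Allocation is revealed one month before implementation, and recruits in the implementation phase are offered counselling and supplied varenicline, whereas control recruits receive a brochure. The two phases could therefore attract people who smoke differently. Baseline cigarettes per day is the most direct covariate for detecting and adjusting for such a shift in this outcome.

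The form fixes what is collected, so this cannot be left to a statistical analysis plan: a count that was never recorded cannot be recovered.

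**Working it through.** The protocol states no sample size or power for this outcome, so there is no figure of its own to reproduce. Two checks apply.

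**1. What the band says about an individual's change**

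Inputs: the four intake bands (Appendix B3, item 2d) and an exact follow-up count *f* (Appendix B4, item 3). A minimum of 1 a day is assumed at baseline because eligibility requires daily smoking. If the baseline lies in the band [L, U], then

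reduction = baseline − *f*, which lies in [L − *f*, U − *f*].

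| Intake band | Decrease certain | Decrease not established | Increase certain |
|---|---|---|---|
| 10 or less (1–10) | *f* = 0 | *f* = 1–10 | *f* ≥ 11 |
| 11–20 | *f* = 0–10 | *f* = 11–20 | *f* ≥ 21 |
| 21–30 | *f* = 0–20 | *f* = 21–30 | *f* ≥ 31 |
| 31 or more | *f* = 0–30 | *f* ≥ 31 | never |

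Examples in the lowest band:

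- *f* = 0: 1 − 0 to 10 − 0, a reduction of 1 to 10.
- *f* = 2: −1 to 8.
- *f* = 5: −4 to 5.
- *f* = 8: −7 to 2.
- *f* = 10: −9 to 0.

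Even where a decrease is certain, its size is known only to within U − L = 9 cigarettes in the three lower bands, and has no upper bound in the top band. With an exact intake count the reduction is a single value for everyone.

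**2. What the band costs as a covariate**

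The protocol gives no distribution of cigarettes per day, so every input here is an assumption: gamma baseline counts with mean 6, 8 or 12 a day and coefficient of variation 0.7; 15% of participants at zero at follow-up; lognormal follow-up noise with SD 0.4. The share of the sample that the loss equals is

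loss = 1 − (1 − R² with exact count) / (1 − R² with bands).

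| Assumed mean | In lowest band | R² exact | R² bands | Loss |
|---|---|---|---|---|
| 6 | 87% | 0.46 | 0.29 | 1 − 0.54/0.71 = 24% |
| 8 | 74% | 0.47 | 0.36 | 1 − 0.53/0.64 = 17% |
| 12 | 52% | 0.46 | 0.40 | 1 − 0.54/0.60 = 10% |

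Re-running the simulation gives the same figures to within about a percentage point. Raising only the noise SD to 0.8 cuts the losses to about 9%, 6% and 3%. With baseline breath CO also in the model (assumed correlation 0.7 with log count), they are about 6%, 4% and 3%.

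Bias was checked under the same base assumptions (noise SD 0.4). With a 10% higher baseline mean in one phase and no treatment effect, adjusting for bands leaves roughly a third of the spurious difference at mean 6, a fifth at mean 8 and a tenth to an eighth at mean 12. Adjusting for the exact count removes essentially all of it.

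**The case against.** The strongest reply is that the outcome itself is sound. Hypothesis iv is a contrast between phases, the listed outcome is a current level, and both phases answer the same follow-up item at the same weeks. This stands. A reader might infer from the mismatched forms that hypothesis iv cannot be tested, or that a fall from 10 to 3 a day would go unseen. Neither follows: the follow-up count of 3 enters the comparison as 3, whatever the baseline record. Only the change score and the covariate are degraded.

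Three other stronger readings also fail.

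- **That only people smoking 10 or fewer a day are affected, and all of them.** No band gives an exact change, and someone in the lowest band who stops completely shows a certain decrease.
- **That nothing can be adjusted for within the lowest band.** Baseline breath CO, time to first cigarette and the other Fagerstrom items vary within it. They are partial substitutes, because none is the baseline value of the outcome. Smoking days per week adds little, since daily smoking is an entry criterion.
- **That phase and calendar time are wholly confounded.** In Table 1, Step 1 implementation and Step 2 control share Year 2, and Step 2 implementation and Step 3 control share Year 3. This overlap helps with time trends. It does not address who chooses to enrol under each offer.

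It may also be said that a follow-up tool is given at baseline, because Estimating process and outcome measures mentions a follow-up smoking use algorithm at that point. The wording is ambiguous, and Tables 2 and 3 do not schedule the follow-up questionnaire at baseline, so it cannot be relied on to supply a count.

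Finally, this is one secondary outcome, with no power claim attached, and the choice of covariates can properly be left to an analysis plan. Both are true, and they limit the importance of the point. The resolution of the data collected is, however, fixed by the form.

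**Conclusion.** The point holds in a limited form. Baseline consumption is banded and follow-up is a number, so individual change and adjustment for baseline cigarettes per day exist only at band level, in all four bands. The between-phase test of hypothesis iv remains available, and the primary outcome is unaffected.

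The cost is precision, plus some protection against a shift in heaviness of smoking between two groups that were not individually randomised. Its size cannot be fixed from the protocol. Under assumed means of 6 to 12 a day it is equivalent to roughly 3% to 24% of the sample for this outcome. The upper end needs light smokers and low follow-up noise; the lower end needs heavier smokers or noisier reports. Clustering is ignored, so these percentages do not translate directly into a number of participants in this design, and 24% should not be read as the expected loss. The change is still worth making because it costs almost nothing.

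**What to change.** In Appendix B3, item 2d, replace the tick-boxes with the exact number of cigarettes smoked per day and derive the Fagerstrom band from it, so the dependence score is preserved. Add the daily count to the description of the intake questionnaire under Estimating process and outcome measures. Use the exact baseline count as a covariate in the cigarettes-per-day comparison.

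The cost is one form field and its database entry, with no added visit time. The drawback is timing. Participants already enrolled have only the band. Since each facility runs its control period first, a change made mid-trial would leave the exact count missing mostly in control-phase enrolments, so the missingness would be tied to phase. The band must then be used for those participants, or an analysis using the band for everyone reported as a sensitivity analysis. The sooner the field is changed, the smaller this imbalance.
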